# Randomized Embolization Trial for NeuroEndocrine Tumor Metastases to the Liver (RETNET): study protocol for a randomized controlled trial

**DOI:** 10.1186/s13063-018-2782-5

**Published:** 2018-07-17

**Keywords:** Neuroendocrine tumor, Embolization, Chemoembolization, Liver metastases

## Abstract

**Background:**

Neuroendocrine tumors (NETs) are the second most common gastrointestinal malignancy after colon cancer. Up to 90% of patients with NETs develop liver metastases, which are a major determinant of symptoms and survival. Current guidelines recommend embolotherapy for progressive or symptomatic NET liver metastases, but the optimal technique among bland embolization, lipiodol chemoembolization, and drug-eluting bead chemoembolization remains unknown and controversial.

**Methods/design:**

A prospective, open-label, multicenter randomized controlled trial will be conducted in patients with progressive or symptomatic unresectable NET liver metastases. Patients will be randomized to treatment with bland embolization, lipiodol chemoembolization, or drug-eluting microsphere chemoembolization, with 60 enrollees per arm. The primary endpoint will be hepatic progression-free survival (HPFS) following initial embolotherapy by RECIST criteria. The sample size is powered to detect an HR of 1.78 for HPFS following chemoembolization compared with bland embolization, which was estimated on the basis of existing retrospective studies. Secondary endpoints include overall progression-free survival, duration of symptom control, quality of life, rate of adverse events, and interval between embolotherapy cycles. Interim safety analyses will be performed at 10 and 30 patients per arm.

**Discussion:**

The RETNET trial is a prospective, multicenter randomized controlled trial designed to determine the optimal embolotherapy technique for NET liver metastases.

**Trial registration:**

ClinicalTrials.gov, NCT02724540. Registered on March 31, 2016.

**Electronic supplementary material:**

The online version of this article (10.1186/s13063-018-2782-5) contains supplementary material, which is available to authorized users.

## Background

Neuroendocrine tumors (NETs) are a heterogeneous family of neoplasms that arise from cells in the gastrointestinal (GI) tract, pancreas, and lung. With an estimated prevalence of > 100,000 in the United States and a steadily increasing incidence over the past quarter century [1], NETs have become the second most common GI malignancy after colon cancer. NET cancer biology has a propensity for the development of liver metastases, which occur in 40–90% of patients [2] and are a major determinant of symptoms and survival. Analysis of National Cancer Institute Surveillance, Epidemiology, and End Results registry data from 1973 to 2004 demonstrated that patients with localized, regional, or distant metastatic disease had median survivals of 223, 111, and 33 months, respectively [1]. With supportive care only, patients with unresectable liver metastases have a 5-year survival of 0–22%. Symptom control and survival outcomes improved in the late 1980s with the introduction of octreotide, a somatostatin analogue used to control hormone secretion-related symptoms. During the past three decades, there has also been widespread refinement and adoption of locoregional transarterial embolotherapy for treatment of NET liver metastases. By selectively embolizing hepatic arterial tumor feeders, metastases are cut off from their vascular supply, whereas the normal liver parenchyma retains viability via perfusion from the portal veins. Studies have demonstrated efficacy of these liver-directed embolotherapies for tumor growth reduction and NET symptom relief, with current 5-year survival rates of over 60% and response rates between 70% and 90% [3–13].

Liver-directed embolotherapy encompasses distinct techniques, including “bland” embolization (BE) using embolic particles instilled via the hepatic artery to cut off tumor blood supply and transarterial chemoembolization (TACE) using either an ethiodized oil emulsion of chemotherapeutic drugs (conventional lipiodol TACE, classical transarterial chemoembolization [cTACE]) or drugs loaded onto embolic microspheres (drug-eluting bead transarterial chemoembolization [DEB-TACE]). Current National Comprehensive Cancer Network, North American Neuroendocrine Tumor Society, and European Neuroendocrine Tumor Society guidelines support embolotherapy for symptomatic or progressive NET liver metastases on the basis of level IIB-3 evidence [14–18], but they offer no recommendation regarding available techniques.

Published studies comparing TACE with bland embolization (BE) have demonstrated heterogeneous and contradictory results, with some studies showing superior survival and/or safety outcomes for one technique [5, 6, 9] and others demonstrating equivalent outcomes [8, 19, 20]. One of the potential contributors to these varying results was ambiguity in the World Health Organization (WHO) 2000/2004 NET pathologic grading systems, which were used in many older studies [4, 6, 7, 9, 12, 21] and have since been replaced by the more objective, reproducible WHO 2010 system. In addition to uncertainty about survival outcomes among embolotherapy techniques, the comparative safety profiles and treatment toxicities also remain controversial. Two retrospective series have suggested higher risks for biliary complications after DEB-TACE [13, 22], but there remains no definitive comparison with lipiodol TACE or BE. The combination of an indeterminate evidence base and lack of specific guideline recommendations have contributed to wide variations in clinical practice, manifesting in equivalent use of available embolotherapy techniques for NET liver metastases in a survey of U.S. interventional radiologists [23].

Given the increasing incidence of NET and ongoing questions regarding an optimal treatment algorithm for NET liver metastases, there is a need for a prospective randomized controlled trial (RCT) to elucidate the optimal embolotherapy technique between transarterial BE and chemoembolization. This article presents the study protocol of a prospective, open-label, multicenter RCT using a parallel group assignment and noninferiority design. The trial aims to determine the optimal embolotherapy modality for NET liver metastases by comparing hepatic progression-free survival (HPFS), treatment toxicities, symptom control, and quality of life.

## Methods/design

### Hypothesis

The primary hypothesis of this study is that HPFS following TACE (lipiodol or DEB-TACE) will be nearly twice as durable as BE (HR, 1.78) for control of NET liver metastases. This will be tested against a null hypothesis of equality among embolization methods, without preconception of ranking.

### Study design

This is an open-label, multicenter, randomized trial comparing three embolotherapy techniques for NET liver metastases: (1) BE, (2) cTACE, and (3) DEB-TACE. The study flowchart is shown in Fig. 1. Anticipated study sites include academic hospitals in the United States, Australia, Canada, France, and Argentina.

**Fig. 1 Fig1:**
[figure not shown]
Study flowchart. *CT* Computed tomography, *MRI* Magnetic resonance imaging, *QOL* Quality of life, *Sx* symptom

This trial will be conducted in accordance with the principles outlined in the Declaration of Helsinki and will follow the Consolidated Standards of Reporting Trials (CONSORT) statement. A Standard Protocol Items: Recommendations for Interventional Trials (SPIRIT) checklist is provided in Additional file 1.

### Study population

Eligible participants will have liver-dominant NET that is symptomatic, progressive, or with a liver tumor burden > 25% of the liver volume without need for documented progression. Patients with extrahepatic disease progression can be enrolled in the study if they have liver-dominant disease based on the assessment of a multidisciplinary NET care team. Concurrent treatment with somatostatin analogues is allowed. No concomitant radiation therapy, chemotherapy (e.g., capecitabine/temozolomide), biologic therapy (e.g., everolimus, sunitinib), or ablation is allowed. Patients also cannot receive these treatments until after the primary endpoint of hepatic progression is reached. All participants will be consented with an institutional review board (IRB)-approved, site-specific informed consent form prior to undergoing any study-related procedures. Detailed inclusion and exclusion criteria are shown in Table 1. A SPIRIT figure is shown in Fig. 2, and a SPIRIT checklist is available in Additional file 1. Patients may be withdrawn from the study for failure to adhere to protocol requirements or withdrawal of consent.

**Table 1 Tab1:** RETNET trial inclusion and exclusion criteria

Inclusion criteria	Exclusion criteria
• Participants aged 18 years and older • Biopsy-proven neuroendocrine tumor with tumor burden dominant in the liver • Measurable metastasis to liver with at least one dimension ≥1.0 cm. Known extrahepatic disease should be limited to lymph nodes of < 2 cm and/or any bone metastases. • Liver tumor burden ≤ 70% of the total liver volume by visual estimate • Not a candidate for surgical resection owing to unresectability, anatomy, anesthesia risk, patient preference • Symptoms uncontrolled by somatostatin analogues OR morphologically progressive tumor by RECIST 1.1 criteria in the liver OR baseline tumor burden > 25% of the liver volume • No plans for the patient to receive other concomitant therapy while on this protocol treatment (other than octreotide or bisphosphonate therapy) • Performance status 0–2 on Zubrod performance scale • Serum creatinine ≤ 2.0 mg/dl • Serum bilirubin ≤2.0 mg/dl • Serum albumin ≥3.0 g/dl • Platelet count ≥ 50,000/μl (corrected if needed) • INR ≤ 1.5 (corrected if needed) • All patients must be informed of the investigational nature of this study and must sign a study-specific informed consent form in accordance with institutional and federal guidelines prior to study entry.	• Pregnant or lactating women may not participate, owing to the embryotoxic effects of protocol treatment. • Women/men of reproductive potential may not participate unless they have agreed to use an effective contraceptive method. • Prior hepatic arterial therapy or hepatic radiation therapy. Prior surgical resection or ablation of liver metastases is acceptable. Patients must be at least 1 month beyond prior chemotherapy, PRRT, ablation, or surgery and must have recovered from all therapy-associated toxicities. • Active infection (symptomatic bacterial and fungal infection, newly diagnosed and/or requiring treatment) • Choledochoenteric anastomosis, transpapillary biliary stent, or sphincterotomy of duodenal papilla • Absolute contraindication to intravenous iodinated contrast agent (history of significant previous contrast agent reaction not mitigated by appropriate premedication) • Allergy to doxorubicin • Contraindications to arteriography and selective visceral catheterization: ○ Severe allergy or intolerance to contrast media, narcotics, sedatives, or atropine * ○* Bleeding diathesis not correctable by usual forms of therapy * ○* Severe peripheral vascular disease precluding catheterization • Contraindications to hepatic artery embolization: * ○* Portal vein occlusion without hepatopedal collateral flow demonstrated by angiography or portal hypertension with hepatofugal flow * ○* Hepatic encephalopathy

*Abbreviations: INR* International normalized ratio, *PRRT* Peptide receptor radionuclide therapy, *RECIST* Response Evaluation Criteria in Solid Tumors, *RETNET* Randomized Embolization Trial for NeuroEndocrine Tumor Metastases to the Liver

**Fig. 2 Fig2:**
[figure not shown]
Standard Protocol Items: Recommendations for Interventional Trials (SPIRIT) figure. *CT* Computed tomography, *MRI* Magnetic resonance imaging

### Investigations and interventions

#### Baseline evaluation

Clinical assessment, patient-reported NET quality of life (European Organization for Research and Treatment of Cancer [EORTC] QLQ-C30 and G.I.NET21 questionnaires) and Carcinoid Symptom Severity Score [24], screening laboratory studies (complete blood count, partial thromboplastin time, internal normalized ratio, comprehensive metabolic profile, tumor markers including chromogranin A), and imaging (abdominal computed tomography [CT] or magnetic resonance imaging [MRI], chest CT) will be performed within 30 days of initial embolotherapy. Patients with tumors without available histologic grading (WHO 2010) must undergo percutaneous biopsy to determine tumor grade. Once the eligibility data forms are completed in the ORACLE database (Oracle, Santa Clara, CA, USA) and baseline images are uploaded to the Imaging Core and undergo a quality control check, the treatment assignment is automatically generated via a built in block randomization program (*see* “Randomization” section below).

#### Embolotherapy technique

BE will be performed with lobar or segmental infusion of microspheres (100–500 μm) to an embolization endpoint of two- to five-heartbeat stasis. Conventional lipiodol TACE will be performed with lobar or segmental infusion of doxorubicin 50 mg, dissolved in 10 ml of diluted iodinated contrast agent, and emulsified with ethiodized oil, followed by embolization with 40–500-μm microspheres. DEB-TACE will be performed with lobar or segmental infusion of drug-eluting microspheres (100–300-μm or 300–500-μm microspheres loaded with doxorubicin per manufacturer’s instructions for use). For all treatment arms, embolotherapy to additional vascular territories will be performed every 4 weeks until the entire tumor burden is treated. The decision for lobar or segmental embolization and nuances of embolotherapy technique will be determined by operator preference.

#### Follow-up evaluation

Follow-up laboratory assays will be performed 3–3.5 weeks after the first embolotherapy session. If the patient remains eligible for further therapy, additional segmental or lobar embolization will be administered every 4 weeks until the entire disease area is adequately addressed. A maximum of four treatments can be performed per treatment cycle.

After the final embolotherapy session of the treatment cycle, serial clinic visits, QOL and NET symptom scores, laboratory assays including tumor marker(s), and triple-phase CT or MRI will be performed at 4–6 weeks posttreatment and then every 3 months ± 4 weeks (Fig. 1). If the patient remains within the eligibility criteria, repeat embolotherapy cycles can be performed when clinically indicated for intrahepatic progression. The second embolotherapy cycle will resume as described above. Total follow-up duration for each enrollee is at least 24 months. After this point, patients without disease progression will continue to receive clinical and imaging follow-up per institutional standard of care for the remaining duration of the trial.

### Study objectives

#### Primary endpoint

The primary endpoint is HPFS from initial embolotherapy by Response Evaluation Criteria in Solid Tumors (RECIST) 1.0 criteria, as determined by blinded central review of follow-up imaging. Because all of the embolization techniques are in common clinical use, there will be no formal interim efficacy analysis.

#### Secondary endpoints

Secondary endpoints include comparisons of the following:Time interval between embolotherapy cycles among embolotherapy techniquesNET symptom-free interval using the Carcinoid Symptom Severity Score among embolotherapy techniquesPatient-reported quality of life (EORTC QLQ-C30) and NET symptom (G.I.NET21) scores among embolotherapy techniquesToxicity and adverse events among embolotherapy techniquesOverall progression-free survival (PFS) by RECIST 1.1 criteria and duration of symptom control between gut and pancreatic NET, as well as among tumor gradesBiomarkers (imaging, laboratory, and/or symptom) for treatment effect in all treatment arms

#### Primary safety endpoint

According to the Society of Interventional Radiology quality improvement guidelines for embolization and chemoembolization, major hepatic complications (biloma, abscess, liver failure) occur following approximately 6% of procedures, and the performance threshold is set at 8% [25]. The overall rate of any complication is 10%, with a performance threshold of 15%. All arms will be monitored for serious adverse events (SAEs) exceeding published thresholds. SAEs are classified as any event that is fatal; life-threatening; requires or prolongs hospital stay; results in persistent or significant disability, congenital anomaly, or birth defect; or an important medical event. Adverse events will also be classified using Common Terminology Criteria for Adverse Events (CTCAE) grading. Liver function test elevations of CTCAE grade 3 or lower and any clinical symptoms attributable to postembolization syndrome will not be reported unless they meet a criterion. All toxicities/events at or above CTCAE grade 4 will be reported. SAEs will be reported to the study sponsor by telephone and study form within 24 hours of the event. Interim safety analyses will be performed by an independent safety monitoring committee, which is composed of three interventional oncologists from institutions not involved in the trial, following accrual of 10 and 30 patients in each arm. A 20% rate of SAEs at these interim analyses will result in closure of the corresponding treatment arm.

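### The reporting exemption for lower-grade liver-function elevations and postembolization symptoms is not limited to SAE reporting, and so conflicts with the planned toxicity comparison between arms

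*Protocol article*

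**What the plan says.** The rule is in the protocol article under Primary safety endpoint: "Liver function test elevations of CTCAE grade 3 or lower and any clinical symptoms attributable to postembolization syndrome will not be reported". It names two categories, liver-function elevations of CTCAE grade 3 or lower and symptoms of postembolization syndrome, and ends with an exception: "any clinical symptoms attributable to postembolization syndrome will not be reported unless they meet a criterion". The criterion is not named. The nearest candidates are the SAE criteria earlier in the same paragraph: "SAEs are classified as any event that is fatal; life-threatening; requires or prolongs hospital stay", followed by disability, congenital anomaly or birth defect, and important medical events.

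Three neighbouring sentences bear on how the rule is read:

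- Just before it: "Adverse events will also be classified using Common Terminology Criteria for Adverse Events (CTCAE) grading".
- Just after it: "All toxicities/events at or above CTCAE grade 4 will be reported".
- Next comes the expedited rule, confined to SAEs: "SAEs will be reported to the study sponsor by telephone and study form within 24 hours of the event".

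Elsewhere, Secondary endpoints lists toxicity and adverse events among techniques as a comparison and sets no grade limit. The Background gives the trial's purpose as finding the best technique by "comparing hepatic progression-free survival (HPFS), treatment toxicities, symptom control, and quality of life". The Discussion expects the results to show which technique, if any, has the better HPFS, the better safety profile, or both.

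**The concern.** The article plans to compare toxicity between arms without restriction, and also tells sites not to report two kinds of toxicity that follow directly from embolizing the liver. It does not say that the second statement is only about what goes to the sponsor as an SAE.

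Two things are at stake. The first is information: if a site takes the rule at face value, non-serious liver-function elevations up to grade 3 and non-serious postembolization symptoms drop out of the comparison. The second is bias: leaving a symptom out depends on someone attributing it to postembolization syndrome, and Study design describes the trial as open-label. The blinded central review covers imaging only. Under-reporting of symptoms could therefore differ by arm. A finding of similar toxicity would then be hard to interpret for these two categories.

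**Working it through.** The article gives no figure for this comparison that could be reproduced, so the check sets its statements side by side.

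**1. What the rule leaves reportable**

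| Event | Reported under the rule as written? |
|---|---|
| Liver-function elevation, grade 4 or higher | Yes |
| Liver-function elevation, grade 3 or lower, meeting a criterion | Yes |
| Liver-function elevation, grade 3 or lower, meeting none | No |
| Postembolization symptom, grade 4 or higher or meeting a criterion | Yes |
| Postembolization symptom, below grade 4 and meeting none | No |
| Other toxicity, grade 1 to 3 | Not expressly excluded |

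The secondary endpoint covers every row. The rule removes the two rows marked No, and the article does not reconcile the two statements.

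**2. Whether the scheduled visits fill the gap**

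Follow-up evaluation gives the first laboratory point: "Follow-up laboratory assays will be performed 3–3.5 weeks after the first embolotherapy session". Assays follow at 4–6 weeks after the final session of the cycle, then every 3 months ± 4 weeks. Clinic visits and symptom scores are first stated at that 4–6 week point. Sessions are 4 weeks apart, with at most four per cycle.

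Take a full cycle, with sessions at weeks 0, 4, 8 and 12:

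- First stated assay: week 3 to 3.5.
- Next stated assay, and first stated clinic visit and symptom score: week 12 + 4 = 16 to week 12 + 6 = 18.
- Interval between the two stated assays: 16 − 3.5 = 12.5 to 18 − 3 = 15 weeks.

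Scheduled assays can therefore show liver-function elevations present on those dates. They cannot show an elevation that rises and resolves between them, and they do not capture symptoms. For such events the article states no other route than adverse-event reporting.

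**3. Illustration of scale, under assumed rates**

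The article gives no rate for either category. Every rate below is an assumption. Inputs: n = 60 per arm (Sample size calculation) and two-sided 5% (assumed here). Arcsine formula:

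h = 2·arcsin√p₂ − 2·arcsin√p₁; power ≈ Φ(h·√(n/2) − 1.96), with √(60/2) = 5.477.

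- 20% versus 40%: h = 1.3694 − 0.9273 = 0.442; 0.442 × 5.477 = 2.42; Φ(0.46) = 0.68.
- 5% versus 10%: h = 0.6435 − 0.4510 = 0.192; 0.1925 × 5.477 = 1.05; Φ(−0.91) = 0.18.

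| Assumed rates | Power |
|---|---|
| 40% vs 60% | 0.60 |
| 30% vs 50% | 0.62 |
| 20% vs 40% | 0.68 |
| 10% vs 20% | 0.34 |
| 5% vs 10% | 0.18 |
| 3% vs 6% | 0.12 |

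If lower-grade events are common and severe ones uncommon, a comparison confined to the severe ones has much less chance of showing a difference. Whether that holds here cannot be learned from the article.

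**The case against.** The strongest reply is that the sentence is about SAE reporting and not data collection. The paragraph runs from SAE monitoring through the SAE definition to 24-hour notification and an SAE-based stopping rule, and not reporting an event is not the same as not recording it. This reading is plausible. But the text does not state it: the rule directly follows the sentence on grading adverse events in general, the grade 4 sentence speaks of toxicities as well as events, and the 24-hour rule comes later and is limited to SAEs.

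A second reply is that a condensed article need not say what the case report form collects. That is true of silence. Here the article makes a positive exclusion that conflicts with its own endpoint.

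Third, liver-function values may be available from scheduled assays, since a metabolic profile is part of the baseline panel and study data go into the trial database. This stands in part, although the article does not name liver-function tests at follow-up.

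Fourth, the article does not say who attributes symptoms to postembolization syndrome. That also stands: differential under-reporting is a risk in an open-label trial, not something the text demonstrates.

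A reader might infer more than the documents support:

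- **That all postembolization symptoms are excluded.** Those meeting a criterion, or of grade 4 or higher, are reported.
- **That arms can be compared only on serious or grade 4 events.** Other grade 1 to 3 toxicities are not expressly excluded. If grade 4 were a general floor, a separate exemption for liver-function elevations up to grade 3 would be redundant.
- **That the comparison loses its main data, or that the events are never recorded.** No rates are given, and the rule speaks of reporting.

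**Conclusion.** The point holds in a limited form. As written, the exemption has no stated scope and conflicts with the unrestricted secondary comparison of toxicity. For two categories, liver-function elevations up to grade 3 and postembolization symptoms below grade 4, only events meeting an undefined criterion would enter that comparison through adverse-event reporting. Scheduled assays may recover part of the first category, but not early transient events, and none of the second.

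The conclusion assumes that sites follow the sentence literally and that no fuller document limits it. If the full protocol already confines it to SAE reporting, what remains is a wording correction in the article. The size of the loss cannot be computed; the power figures show only how such a restriction could matter under assumed rates. The sponsor should make the change, but it bears on a secondary comparison and leaves the primary analysis untouched.

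**What to change.** Amend the sentence under Primary safety endpoint in three respects:

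1. Limit the exemption to SAE or expedited reporting to the sponsor.
2. Define the criterion as the SAE criteria listed in that paragraph.
3. State that liver-function elevations, graded by CTCAE from the assays already scheduled, and postembolization symptoms, with their CTCAE grade, are recorded in all arms regardless of attribution and enter the secondary toxicity comparison.

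Recording symptoms whatever their attribution removes the open-label judgement from the decision to include them.

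The cost is a clarified sentence or two and a small extra data-entry burden at sites. No treatment, sample size or scheduled test changes. Because enrolment was under way when the article was submitted, the change should be made promptly: symptoms that were not recorded cannot be reliably reconstructed later.
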